## Abstract

**Background:**

Early intensive blood pressure (BP) lowering remains the most promising treatment for acute intracerebral hemorrhage (ICH), despite discordant results between clinical trials and potential variation in the treatment effects by approach to control BP. As the third in a series of clinical trials on this topic, the INTEnsive care bundle with blood pressure Reduction in Acute Cerebral hemorrhage Trial (INTERACT3) aims to determine the effectiveness of a goal-directed care bundle protocol of early physiological control (intensive BP lowering, glycemic control, and pyrexia treatment) and reversal of anticoagulation, in acute ICH.

**Methods:**

INTERACT3 is a pragmatic, international, multicenter, stepped-wedge (4 phases/3 steps), cluster-randomized controlled trial to determine the effectiveness of a multifaceted care package in adult (age ≥ 18 years) patients (target 8360) with acute ICH (< 6 h of onset) recruited from 110 hospitals (average of 19 consecutive patients per phase) in low- and middle-income countries. After a control phase, each hospital implements the intervention (intensive BP lowering, target systolic < 140 mmHg; glucose control, target 6.1–7.8 mmol/L and 7.8–10.0 mmol/L in those without and with diabetes mellitus, respectively; anti-pyrexia treatment to target body temperature ≤ 37.5 °C; and reversal of anticoagulation, target international normalized ratio < 1.5 within 1 h). Information will be obtained on demographic and baseline clinical characteristics, in-hospital management, and 7-day outcomes. Central trained blinded assessors will conduct telephone interviews to assess physical function and health-related quality of life at 6 months. The primary outcome is the modified Rankin scale (mRS) at 6 months analyzed using ordinal logistic regression. The sample size of 8360 subjects provides 90% power (*α* = 0.05) to detect a 5.6% absolute improvement (shift) in the primary outcome of the intervention versus control standard care, with various assumptions.

**Discussion:**

As the largest clinical trial in acute ICH, INTERACT3 is on schedule to provide an assessment of the effectiveness of a widely applicable goal-directed care bundle for a serious condition in which a clearly proven treatment has yet to be established.

**Trial registration:**

ClinicalTrials.gov NCT03209258. Registered on 1 July 2017. Chinese Trial Registry ChiCTR-IOC-17011787. Registered on 28 June 2017

**Supplementary Information:**

The online version contains supplementary material available at 10.1186/s13063-021-05881-7.

## Administrative information

Note: the numbers in curly brackets in this protocol refer to SPIRIT checklist item numbers. The order of the items has been modified to group similar items (see http://www.equator-network.org/reporting-guidelines/spirit-2727-statement-defining-standard-protocol-items-for-clinical-trials/).

## Introduction

### Background and rationale {6a}

Acute spontaneous intracerebral hemorrhage (ICH) is the most severe type of stroke, for which two thirds of patients either die or are disabled, and where the overall rates and outcomes have remained relatively stable in recent decades [1, 2]. Although ICH accounts for approximately 10–20% of strokes in high-income countries, proportional frequencies and rates are much higher in low- and middle-income countries (LMICs) causing considerable personal, social, and economic burden in large high-risk populations [3–5].

Although slow progress has been made in reliably establishing effective medical (and surgical) treatments for ICH, intensive blood pressure (BP) lowering is the most attractive as it is relatively low-cost, widely applicable, and supported by strong epidemiological data for the frequency and prognostic significance of hypertension in ICH [6]. This treatment appears safe and effective when given early after the onset of ICH [7] when most of the bleeding occurs, defined as hematoma growth or expansion [8]. Thus, BP lowering in the context of other active, supported, and organized care [9, 10] could provide large absolute benefits even if the benefits to individual patients are modest. Yet, there are ongoing concerns over the size of potential benefits and harms [11] across different types of patients, which influence guideline recommendations and the unifying of clinical practice [12]. There is also uncertainty over the benefits of controlling other abnormal physiological variables, such as hyperglycemia [13, 14] and pyrexia [15], as well in the reversal of anticoagulation [16], which are associated with hematoma growth and adverse outcomes [17, 18], but where there are considerable challenges to providing the necessary evidence from adequately powered randomized studies.

Clustering interventions together as part of a care bundle have shown encouraging results. For example, the Australian Quality in Acute Stroke Care (QASC) cluster trial [19] showed that a protocol to manage fever, hyperglycemia, and assessments of swallowing function improved recovery for patients with acute stroke, while a quality improvement “before-and-after” evaluation of protocol involving anticoagulation reversal, intensive BP lowering, and rapid triage and access to neurosurgery and critical care showed improved survival in patients with ICH admitted to hospitals in Greater Manchester, UK [20]. Our analyses of the second phase of INTEnsive blood pressure Reduction in Acute Cerebral hemorrhage Trial (INTERACT2) showed that the scoring of abnormal baseline variables covering BP, glucose, body temperature, and prior use of anticoagulants independently predicted poor outcome in ICH [21].

We therefore initiated the third INTEnsive care bundle with blood pressure Reduction in Acute Cerebral hemorrhage Trial (INTERACT3) with collaborators in 10 Asian, Latin American, and African countries (Appendix 1) to determine the effectiveness of a goal-directed care bundle of active management involving early physiological control (intensive BP lowering, glycemic control, and pyrexia treatment) and reversal of anticoagulation, compared against usual standard of care. Using a pragmatic, one direction, stepped-wedge, cluster-randomized controlled trial design, the aims are to provide evidence of the applicability of a readily scalable, goal-directed protocol that could be widely applied in clinical practice, while also providing information on the effectiveness of particular components and across certain characteristics of patients. Herein, we report the final version of the trial protocol, compliant with the Standard Protocol Items: Recommendations for Interventional Trials (SPIRIT) reporting guideline (Appendix 2).

## Objectives {7}

### Hypothesis

A goal-directed care bundle of active management involving early physiological control (intensive BP lowering, glycemic control, and pyrexia treatment) and reversal of anticoagulation improves functional outcome after acute ICH.

### Research questions

Does a goal-directed care bundle of active management involving early physiological control (intensive BP lowering, glycemic control, and pyrexia treatment) and reversal of anticoagulation improve functional outcome after acute ICH compared to usual standard of care (the null hypothesis is that there is no difference in functional outcomes between treatment groups)?Does a care bundle improve other clinical outcome measures of death and dependency, separately on death and physical function, health-related quality of life (HRQoL), days of hospitalization, and living circumstances, compared to usual care?Does a care bundle reduce hematoma growth and perihematomal edema?Is there heterogeneity in the treatment effects across particular patient characteristics?Are there clinical benefits associated with the separate components of the care bundle?What factors support or impede the integration of a care bundle protocol for ICH in hospital practice?What are the costs of implementing the care bundle?

## Trial design {8}

The INTERACT3 study is an international, multicenter, prospective, stepped-wedge, cluster-randomized controlled, blinded outcome assessed (PROBE) trial, which is being conducted through a network of investigators in LMICs. After participating hospital sites commence in a usual care “control” phase, they progressively transfer to the intervention (care bundle) at pre-determined stages through random allocation into 3 groups (Fig. 1). In each phase, hospitals aim to reach an average target of 19 consecutive ICH patients who fulfill the eligibility criteria, but this number may vary from 1 to 50 patients according to service configuration and patient volumes. However, each phase has a 3-month time limit, to ensure that the intervention period of the study is completed over 12 months. The study design is summarized in Fig. 2.

**Fig. 1 Fig1:**
[figure not shown]
Stepped-wedge design

**Fig. 2 Fig2:**
[figure not shown]
Study schema

## Methods: participants, interventions, and outcomes

### Study setting {9}

The trial is being conducted in approximately 110 hospitals in 9 LMICs: Brazil, China, India, Mexico, Nigeria, Pakistan, Peru, Sri Lanka, and Vietnam, and one high-income country, Chile.

### Eligibility criteria {10}

#### Hospital sites

Hospitals are eligible if they do not have any organizational protocols for the management of ICH, or if they use protocols different to those proposed in the study and are comfortable about switching to the proposed interventional bundle. All patients with acute ICH who present to participating sites are included on a register during the study period, with those fulfilling the eligibility criteria included in the study. Brief details of all patients with acute ICH who are screened but not included, as well as those recruited, are recorded on the screening/enrolment form. All eligible patients are provided with an approved patient information sheet (PIS) or patient responsible information sheet (PRIS) and consent form (CF). A participant is anyone for whom consent is obtained for permission to collect their medical and personal information, and to be contacted at 6 months for a follow-up assessment of their health status.

### Study patient characteristics

Patients are eligible to participate if they:
Are an adult (aged ≥18 years)Have an acute stroke syndrome due to presumed spontaneous ICH, defined as the sudden occurrence of bleeding into the parenchyma of the brain that may extend into the ventricles and, in rare cases, into the subarachnoid space, confirmed by clinical history and on CT brain imagingPresent within 6 hours of the onset of symptoms

Patients with an ICH that is presumed secondary to a medical treatment, for example antithrombotic or anticoagulation therapy, are eligible, but those that follow treatment with intravenous thrombolysis or endovascular thrombectomy for acute ischemic stroke are ineligible. If the precise timing of the first onset of symptoms or signs of the qualifying event are unknown, then the time of onset is taken as the last time at which the patient was known to be well.

Patients are excluded if they:
Have definite evidence that the ICH is secondary to a structural abnormality in the brain (e.g., an arteriovenous malformation [AVM], intracranial aneurysm, tumor, trauma, or previous cerebral infarction)Have had recent thrombolysis/thrombectomyHave a high likelihood that the patient will not adhere to the study treatment and/or follow-up regimen

In each case, the decision about a patient’s eligibility is based upon the attending clinician’s interpretation of these eligibility criteria.

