#### Strategies to improve adherence to the intervention {11c}

The intervention protocol is given to investigators only after completion of control phase. An online training is organized for each site before starting the intervention. Regular intervention quality reports are provided to each site during intervention phase, and there is remote communication and on-site monitoring to improve the adherence to the intervention. Moreover, a process evaluation, designed to gain insights into the barriers and facilitators to change systems of care and implementation of the protocol, is undertaken through formative stakeholder engagement interviews during the course of the study.

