### Recruitment {15}

All eligible ICH patients who present to each participating hospital from the start date are prospectively and consecutively enrolled into the study.

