### Implementation {16c}

In phase 1, all hospitals will be observed under usual care “control” conditions according to usual management of ICH patients. In phase 2, the first cluster of hospitals (group 1) will start implementing the intervention (care bundle), and then sequentially, groups 2 and 3 will start implementing the interventional package in phases 3 and 4, respectively, so that by phase 4, all hospitals will be receiving the intervention, with those in group 1 having the intervention for longest and those in group 3, the shortest. Once the site has completed the necessary control usual care observational period, they will receive training on the application of the care bundle intervention during the study. The site investigator will be informed to pause enrolment when the patient number or study duration in control phase has reached the pre-specified target, and then will be instructed to transfer over to the intervention phase after a recruitment interval of 7–10 days.

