## Assignment of interventions: blinding

### Who will be blinded {17a}

The treatment is open label to both investigators and patients at sites. All other investigators, statisticians, and endpoint assessors are blind to the treatment allocation, who are trained to collect outcome measures by telephone at 6 months.

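### The non-adherence exclusion has a study-treatment limb with nothing to act on in control phases and is applied by unblinded clinicians, so case selection can differ by arm

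*Protocol article*

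**What the plan says.** Under Study patient characteristics, the protocol article lists as an exclusion "a high likelihood that the patient will not adhere to the study treatment and/or follow-up regimen". It gives no definition or threshold, and adds that "the decision about a patient’s eligibility is based upon the attending clinician’s interpretation of these eligibility criteria".

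Five other statements bear on how that criterion works:

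- Who will be blinded {17a}: "The treatment is open label to both investigators and patients at sites".
- Implementation {16c}: "In phase 1, all hospitals will be observed under usual care “control” conditions". Groups 1, 2 and 3 then switch in phases 2, 3 and 4.
- Strategies to improve adherence {11c}: "The intervention protocol is given to investigators only after completion of control phase".
- Recruitment {15}: "All eligible ICH patients who present to each participating hospital from the start date are prospectively and consecutively enrolled into the study".
- Eligibility criteria {10}, Hospital sites: all acute ICH patients are entered on a register, and "Brief details of all patients with acute ICH who are screened but not included, as well as those recruited, are recorded".

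The primary model (Statistical methods {20a}) contains trial phase, arm and site size. Prognostic variables enter in sensitivity analyses.

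**The concern.** The criterion has two limbs. Likely non-adherence to follow-up can be judged in any phase. Likely non-adherence to the study treatment cannot be judged in a control phase: care there is whatever the hospital usually does, and the clinician does not yet hold the bundle protocol. After the switch the same clinician has a study treatment in view and an open-ended reason for leaving a patient out. The person making that judgement knows the arm before each enrolment.

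If the study-treatment limb is used, the intervention-phase sample is filtered in a way the control-phase sample was not. Randomising sites to a switching time does not prevent this, and a model with phase, arm and site size does not correct it. Blinded assessment at 6 months protects the measurement of the outcome, not the composition of the arms.

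The limb also appears to do no useful work. Analysis is by intention to treat, and Criteria for discontinuing or modifying allocated interventions {11b} already lets hospitals alter or omit parts of the bundle on clinical grounds. A patient who may not complete it can stay in the trial.

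**Working it through.** **The plan's own figures.** From Sample size {14}: 110 × 4 × 19 = 8360, and 18 / 0.95 = 18.95, rounded to 19. The control mRS distribution gives 16.6 + 19.0 + 8.0 + 12.0 = 55.6% with mRS 3–6. Control odds are 0.556 / 0.444 = 1.252; times 0.80 this is 1.002, or 50.05%, a drop of 5.55 points and a relative risk of 0.900. All agree with the article.

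Power was checked with a stepped-wedge generalised least squares variance: 36/37/37 sites per group, 4 periods, 18 evaluable patients per site-phase, constant ICC 0.044. The per-patient variance of the ordinal log odds ratio was 3 / (1 − Σp̄³) = 3 / 0.9728, where p̄ is the mean of the two arms' category probabilities. The standard error is 0.0686. Power is Φ(0.2231 / 0.0686 − 1.96) = 90.2%, against the stated 90%. The sample size is not in question.

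**Effect of arm-dependent exclusion.** Let x be the fraction of otherwise eligible patients left out in intervention phases only, and q their risk of mRS 3–6. Neither is in the documents; both are assumptions. With no true effect:

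- intervention rate = (0.556 − xq) / (1 − x)
- shift = x(q − 0.556) / (1 − x)

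The second line fixes the sign. The shift favours the bundle only if those left out are at higher than average risk (q above 0.556). If they are at lower risk, it goes against the bundle.

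At x = 5%:

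- q = 1.0: (0.556 − 0.050) / 0.95 = 53.3%
- q = 0.9: (0.556 − 0.045) / 0.95 = 53.8%
- q = 0.7: (0.556 − 0.035) / 0.95 = 54.8%

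| x | q | Rate | Shift (points) | Odds ratio | False-positive rate |
|---|---|---|---|---|---|
| 1% | 0.7 | 55.5% | 0.15 | 0.994 | 5.1% |
| 1% | 0.9 | 55.3% | 0.35 | 0.986 | 5.5% |
| 1% | 1.0 | 55.2% | 0.45 | 0.982 | 5.8% |
| 2% | 0.7 | 55.3% | 0.29 | 0.988 | 5.3% |
| 2% | 0.9 | 54.9% | 0.70 | 0.972 | 7.0% |
| 2% | 1.0 | 54.7% | 0.91 | 0.964 | 8.3% |
| 5% | 0.7 | 54.8% | 0.76 | 0.970 | 7.3% |
| 5% | 0.9 | 53.8% | 1.81 | 0.930 | 18.7% |
| 5% | 1.0 | 53.3% | 2.34 | 0.910 | 27.9% |

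The false-positive rate is the two-sided probability that a normal statistic with mean |log OR| / 0.0686 exceeds 1.96 in absolute value. It treats the odds ratio at the mRS 3–6 cut as the common odds ratio, so it is approximate. A purely binary analysis gives 15.3% in place of 18.7% for x = 5%, q = 0.9.

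**What would imitate the whole design effect.** Setting the rate to 0.50 gives x = 0.056 / (q − 0.5), that is 28%, 19%, 14% and 11% at q = 0.7, 0.8, 0.9 and 1.0.

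**The case against.** The strongest reply is that this is the ordinary selection risk of any open-label cluster trial, attached to a stock exclusion phrase. Several parts of it stand.

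- A reader might infer that the two arms have different eligibility rules. They do not: there is one list without a phase qualifier, and only its application can differ. The follow-up limb may even remove some of the same patients in control phases.
- A reader might infer that the sickest patients would be dropped, so that selection would imitate a benefit. The documents never link the criterion to moribund patients or to limits on care. Likely non-adherers could equally be mild cases expected to leave early, which would bias against the bundle.
- A reader might see a contradiction with consecutive enrolment. There is none: that commitment covers eligible patients, so it takes effect after this judgement. For the same reason it is no safeguard here.
- Some mitigation is already planned. The register can reveal uneven exclusion, NIHSS and GCS are collected at baseline, and prognostic-variable sensitivity analyses would reduce bias from measured severity. They would not remove bias from unmeasured factors.
- Staff deliver the bundle, under cluster guardian consent, so patient adherence may seldom be the deciding matter. That makes frequent use of the limb less likely, and it also leaves little reason to keep it.

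A further objection is that changing the criterion mid-trial would itself create a difference between arms, because each site moves one way from control to intervention. This largely fails. The deleted limb had nothing to act on in control phases, so removing it brings later enrolment into line with the rule that effectively applied there.

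**Conclusion.** The point holds as a weakness in the eligibility wording: an undefined criterion, one limb of which can operate only after the switch, is applied by clinicians who know the arm. Selection can differ by arm; the article does not show that it does. It gives no exclusion rate, so direction and size are unknown.

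The table assumes exclusion in intervention phases only, no true effect, and chosen values of x and q. The rows with q = 1.0 are an upper bound for each x. At 1–2% the distortion is under one point. At 5% it ranges from 0.76 to 2.34 points, or 14% to 42% of the 5.6-point target (0.76 / 5.6 and 2.34 / 5.6). Imitating the full target would take 11–28% differential exclusion, and nothing in the article suggests that. The wording is worth correcting and the exclusions worth checking; this is not evidence that the result will be biased.

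**What to change.** **Remaining enrolment.** Delete the reference to study treatment, so that the criterion rests on follow-up alone in every phase, and record the date on which each site adopts the change.

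**All patients.** From the existing register and screening form, compare the share of screened patients excluded, and any recorded reasons, between control and intervention phases within site. Read the result alongside the prognostic-variable sensitivity analysis already planned, with baseline NIHSS and GCS among the variables. Add a sensitivity analysis by enrolment before or after the change.

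**Cost.** A minor amendment, which under the article's amendment section can take effect only after ethics review, and a notice to sites. Less adherent patients may dilute the effect slightly, which suits a pragmatic intention-to-treat trial. The new wording cannot reach patients already enrolled: 5917 of 8360 (71%) by 31 December 2020. For them the comparison of exclusions has to carry the weight, and it is limited to the brief details recorded at screening.

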### Consent process {26a}

Each participating site must obtain written approval(s) from their hospital research ethics committee (EC) (e.g., institutional review board [IRB]), and any other relevant regional or national body, before patient recruitment commences (Appendix 3). A variable, mixed consent process is used, according to local/national rules and regulations:
Cluster guardian consent or appropriate approval (e.g., signed by the General Manager or Chief Executive of the hospital, or Head of Neurology/Neurosurgery/Stroke Department) for patients to receive the randomized care bundle to be implemented for patients acute ICH in the Emergency Department, Stroke Unit, Intensive Care Unit, or Neurology/Neurosurgery WardsIndividual standard consent for the collection of data through in-person assessment and data extraction from medical records during the hospital stay and follow-up, and for release of personalized information for research purposes to allow centralized follow-up at 6 months following admission

### Additional consent provisions for collection and use of participant data and biological specimens {26b}

The study consent process includes permission for additional analysis of the collected data for systematic reviews and individual patient data pooling projects. In a subset of 1000 consecutive patients across sites, all brain imaging over a 7–10-day period are collected and uploaded in Digital Imaging and Communications in Medicine (DICOM) format for analysis of the characteristics of the ICH and underlying brain structure at a core imaging laboratory at The George Institute for Global Health (TGI), Sydney, Australia. No biological specimens are collected.

